## Methods

### Study Design

The MEA-WCVD is a prospective, observational, multicentric international study. This publication will focus on the available Tunisian cohort across all governorates of Tunisia, representing patients from all governorates across the public and private health care sectors.

The study aims to enroll at least 2000 female patients from Tunisia, with the participation of hospital and private cardiologists who agree to the study protocol.

**Oversight and Leadership**

The protocol for the MEA-WCVD was approved by the Tunisian Society of Cardiology and Cardiovascular Surgery and coordinated by a team headed by 2 expert female cardiologists.

### Inclusion and Exclusion Criteria

Patients (men and women) are officially enrolled in the MEA-WCVD study only if they are aged >18 years and have at least 1 of the following 4 diagnoses: HF, AF, IHD, or VHD.

Individuals are excluded if they present with CVDs other than the 4 target conditions. Additionally, patients who are unable to provide informed consent—due to cognitive impairment, communication barriers, or other medical or legal reasons—or those who explicitly refuse to participate in the study are also excluded.

### Clinical Assessment and Data Collection

During the office visit, the physician completes the electronic case report form (eCRF) of the registry after the patient’s approval according to the inclusion criteria.

To ensure the accuracy and completeness of the data, all centers involved in data collection adhere to standardized protocols for data entry, with regular training sessions provided to research personnel.

The eCRF is structured into 2 main sections. The first is a common data module that includes a comprehensive set of items pertaining to each patient’s sociodemographic profile and general clinical background. This encompasses variables such as age, sex, level of education, type of health insurance, socioeconomic status, degree of financial or physical dependence, and smoking status. Additionally, it records information on cardiovascular risk factors (eg, hypertension, diabetes, or dyslipidemia), past cerebro-cardiovascular events (such as stroke or myocardial infarction), coexisting pulmonary diseases, thyroid disorders (hypothyroidism or hyperthyroidism), and any history of cancer and related treatments. Key laboratory data such as creatinine and hemoglobin levels are also collected to assess renal function and anemia status, both of which are important prognostic factors in cardiovascular care.

The second part of the eCRF is diagnosis specific and tailored according to the patient’s primary inclusion diagnosis (HF, AF, IHD, or VHD). For each condition, this section captures detailed clinical information, including the etiology, findings from relevant imaging and laboratory tests, the use of guideline-directed medical therapy, occurrence of complications, and aspects related to medication adherence and reported side effects. This diagnosis-specific approach allows for a nuanced evaluation of each disease entity and facilitates meaningful comparisons between male and female patients across the MEA region.

The study began with an initial 75-day enrollment phase, which took place from May 2023 to July 2023. During this phase, eligible participants were identified and enrolled in the study. After the enrollment phase, a planned 1-year follow-up period will be conducted to analyze the outcomes associated with the treatment. This follow-up will be carried out through patient visits to health care centers. The 1-year follow-up period will allow for the evaluation of both short- and long-term treatment effects, contributing to a more comprehensive understanding of the study’s outcomes. The protocol for the MEA-WCVD was approved by the Tunisian Society of Cardiology and Cardiovascular Surgery and coordinated by a team headed by 2 expert female cardiologists.

### Ethical Considerations

This study is conducted in compliance with the principles outlined in the Declaration of Helsinki. The MEA-WCVD (ClinicalTrials.gov ID: NCT05869214) received ethics approval from the South Tunisian Persons’ Protection Committee (0496/2023). The protocol was reviewed and approved as a multicenter study involving both hospital-based and private practice cardiology consultations.

All eligible participants are enrolled only after providing written informed consent during a single outpatient cardiology visit. Investigators ensure that participants fully understand the objectives of the registry, the voluntary nature of their participation, and their right to withdraw at any time without any impact on their medical care.

Data collected via the eCRF include anonymized and pseudonymized identifiers. No identifiable personal data (eg, names, addresses, or national IDs) are stored in the analysis database. All data are securely transferred and stored in a centralized, certified, and encrypted database managed by the contract research organization (Eshmoun, Tunisia).

No financial or material compensation is provided to participants. Participation in the study is voluntary, and no incentives or reimbursements are offered to avoid coercion or bias.

No identifiable photographs, images, or multimedia files of participants are included in this manuscript.

### Statistics

Data will be analyzed using SPSS (version 25; IBM Corp). To explore gender disparities in cardiovascular health outcomes and treatment effectiveness, data will be stratified by gender during analysis.

For the descriptive analyses, the Kolmogorov-Smirnov normality test will be performed for quantitative variables. Means and SDs will be used to describe quantitative variables when they are normally distributed. Otherwise, medians and IQRs will be used. Qualitative variables will be presented as numbers and proportions.

To compare frequencies based on gender, the Pearson chi-square test will be used when the application conditions are verified. Otherwise, the Fisher exact test will be used. To compare means based on gender, the Student 2-tailed *t* test for independent samples will be used when the 2 quantitative variables are normally distributed. If at least one variable is not normally distributed, the Mann-Whitney *U* test will be used. *P* values of less than .05 will be considered statistically significant.

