## Results

The MEA-WCVD study was officially funded in April 2023, with data collection commencing in May 2023. By July 2023, a total of 15,366 participants had been enrolled across 25 centers. The study plans to complete a 1-year follow-up by July 2024, after which data analysis will begin. The primary results are expected to be published in March 2025.

This study seeks to establish the largest registry in the MEA region for HF, AF, IHD, and VHD. By examining these conditions, the study aims to provide valuable insights into regional demographic trends, clinical management practices, and patient adherence to current medical guidelines. The findings will be pivotal in shaping future health care strategies and improving the management of CVDs in the region.

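### A normality pretest chooses between t test and Mann-Whitney; at 15,366 patients most whole-cohort continuous variables will fail it for reasons irrelevant to comparing means

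*Protocol article*

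**What the plan says.** All of the rule stands in the Statistics section of the protocol article.

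- Pretest: "the Kolmogorov-Smirnov normality test will be performed for quantitative variables". No other normality test is named.
- Summary: "Means and SDs will be used to describe quantitative variables when they are normally distributed". "Otherwise, medians and IQRs will be used".
- Comparison when both distributions are normal: "To compare means based on gender, the Student 2-tailed" t test for independent samples.
- Comparison otherwise: "If at least one variable is not normally distributed, the Mann-Whitney" U test.
- Significance: P "values of less than .05 will be considered statistically significant". No separate level is given for the pretest.

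On size, the Results section reports that "a total of 15,366 participants had been enrolled across 25 centers", and Study Design states: "The study aims to enroll at least 2000 female patients from Tunisia". The split by sex is not given. Age, creatinine and hemoglobin belong to the common module of the case report form, which is completed for every patient.

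**The concern.** A normality test asks whether the data depart detectably from a normal curve. The t test needs something else: that the sample means be close to normal, which large samples secure even for skewed data. As n grows, the pretest becomes more sensitive while the condition it is meant to protect becomes easier to meet. In a registry of this size, whether a variable passes depends mainly on the number of patients and the precision of recording, not on whether means are a sensible summary.

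The second branch has its own fault. The sentence that introduces both tests sets the task of comparing means by sex, but Mann-Whitney addresses whether values in one group tend to exceed those in the other. It can reject when the means are equal and only spread or shape differs. With a P value as the only stated criterion, such a result could be reported as a sex difference in the mean.

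**Working it through.** The article gives no figure to reproduce, so the check is how often the rule would reject normality.

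**Inputs.** From the documents: n = 15,366; at least 2,000 Tunisian women; level .05. Assumed: an equal sex split, 15,366 / 2 = 7,683; the .05 level also applies to the pretest; the means, SDs and shapes below. The article does not say whether the Kolmogorov-Smirnov test is used with the Lilliefors correction (needed when mean and SD are estimated from the data) or without, so both are shown.

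**Step 1: tolerated deviation.** The 5% critical value for the largest gap between observed and fitted cumulative distributions is 1.358/√n uncorrected and about 0.886/√n with Lilliefors.

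- n = 200: 0.0960 and 0.0626
- n = 2,000: 0.0304 and 0.0198
- n = 7,683: 0.0155 and 0.0101
- n = 15,366: 0.0110 and 0.0071

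**Step 2: what rounding alone does.** Rounding a normal variable with standard deviation SD to units of h creates steps. At the centre, half a step is about 0.5 × h / (SD × √(2π)).

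- Age in whole years, SD 12: 0.5 × 1 / (12 × 2.507) = 0.0166. This exceeds every critical value at 7,683 and 15,366.
- Hemoglobin to 0.1, SD 1.8: 0.5 × 0.1 / (1.8 × 2.507) = 0.0111. This exceeds both values at 15,366, but at 7,683 only the Lilliefors one.

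**Step 3: simulated rejection rates.** 400 samples per cell, Lilliefors critical values obtained by simulation; entries are Lilliefors / uncorrected.

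| Variable | n = 200 | n = 2,000 | n = 7,683 | n = 15,366 |
|---|---|---|---|---|
| Exactly normal, unrounded | 3% / 0% | 4% / 0% | 6% / 0% | 4% / 0% |
| Normal age, whole years, SD 12 | 16% / 0% | 100% / 20% | 100% / 100% | 100% / 100% |
| Normal hemoglobin, to 0.1, SD 1.8 | 10% / 0% | 70% / 2% | 100% / 68% | 100% / 100% |
| Gamma, skewness 0.1 | 6% / 0% | 18% / 0% | 57% / 5% | 82% / 20% |
| Gamma, skewness 0.2 | 12% / 0% | 64% / 5% | 99% / 67% | 100% / 98% |
| t, 20 degrees of freedom | 8% / 0% | 20% / 0% | 76% / 6% | 97% / 34% |
| Lognormal, log-SD 0.4 (creatinine-like) | 98% / 58% | 100% / 100% | 100% / 100% | 100% / 100% |

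The first row shows that the age and hemoglobin failures come from rounding, since the underlying data are exactly normal.

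**Step 4: is the pretest needed?** At 2,000 per sex (4,000 samples), the large-sample 95% CI for a mean difference with unequal-variance standard error covered the truth in 94.8% of samples for gamma data with skewness 1 and 94.7% for lognormal data with log-SD 0.4. Inference on means is valid without the pretest.

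**Step 5: does Mann-Whitney compare means?** Take two lognormal groups, both with mean 1 and with log-SD 0.4 and 0.3. Their medians are exp(−0.4²/2) = 0.923 and exp(−0.3²/2) = 0.956. Over repeated simulation runs, Mann-Whitney rejected in 86% to 90% of samples at 2,000 per sex and in 100% at 7,683. Welch rejected in 3% to 5%, as it should when the means are equal.

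**The case against.** The strongest defence is that no invalid result follows. Medians, IQRs and Mann-Whitney are legitimate, and for skewed creatinine the median is a sensible summary. The hypothesis and anticipated findings concern diagnostic work-up, procedures, guideline therapy and insurance; these are mainly proportions, compared by chi-square or Fisher tests that the rule does not touch. No continuous outcome is named. All of this stands and limits the impact.

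Some stronger readings are tempting but not supported:

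- *The pretest is why no mean difference will be estimated.* The section promises neither an effect estimate nor a CI in either branch; the t-test branch also ends in a P value. What the pretest removes is the group means and SDs. The abstract's Methods also name multivariable regression, which could give adjusted differences, although no continuous outcome is attached to it.
- *Readers would see no size of effect.* Data are stratified by gender and medians with IQRs are shown, so a difference would be visible, though without an interval.
- *Every variable fails.* With the uncorrected test at 7,683, skewness of 0.1 is rejected in only 5% of samples and rounded hemoglobin in 68%. At 2,000, rounded age is rejected in 20%.
- *The same variable will be summarised differently across disease groups.* This could happen if the test were repeated by diagnosis, but the section stratifies by gender only.

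It is also fair that the test is introduced under the descriptive analyses, and that the sentence choosing the comparison says only that variables are normally distributed. Reading Kolmogorov-Smirnov at 5% as the deciding test is an inference, but the natural one, since no other criterion is offered.

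**Conclusion.** The point holds within limits. The rule is stated in full and fixed badly; it is not a detail left to another document. For continuous variables recorded on the whole cohort or on each sex as a whole, it will mostly reject normality because of rounding or mild skew that does not matter for a t test. Age fails in 100% of samples under both versions of the test at 7,683 and 15,366. Creatinine-like data also always fail; hemoglobin fails in 68% to 100%. Near-normal variables under the uncorrected test, and smaller groups, may pass. The replacement test is then described as comparing means, which it does not do.

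The conclusion rests on an equal sex split, a 5% pretest and the assumed SDs and shapes. It concerns continuous descriptors and laboratory values, not the largely categorical management comparisons. The change should be made, but the rule does not threaten the registry's main objective.

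**What to change.** In the Statistics section:

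1. Delete the normality pretest and the sentences that depend on it.
2. Report both mean (SD) and median (IQR) by sex for each quantitative variable.
3. Compare the sexes by mean difference with 95% CI, from a Welch t test or linear regression with robust standard errors.
4. For laboratory values named in advance as skewed, such as creatinine, analyse the log scale and report the ratio of geometric means with 95% CI. Make this choice from subject knowledge, not from a test on the data.
5. If Mann-Whitney is kept for any variable, describe it as a comparison of distributions rather than of means.

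The cost is a change of wording, a little extra analysis in the software already planned, and slightly longer tables. No new data are needed and the conduct of the study does not change. It should be settled before the tables of continuous variables are finalised.

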**Methods:**

The MEA-WCVD is a prospective, multicenter, observational study enrolling consecutive patients aged ≥18 years with diagnosed HF, AF, IHD, or VHD across 25 tertiary care centers. Participants provide informed consent during a single visit, and trained investigators collect sociodemographic, clinical, and treatment data via electronic case report forms. The electronic case report form captures general characteristics (age, gender, and comorbidities) and diagnosis-specific details (imaging, guideline-based therapies, and complications). Data are stored in a centralized, contract research organization–managed database (Eshmoun-Clinical Research, Tunisia). An initial 75-day enrollment phase (May 2023-July 2023) is followed by a planned 1-year follow-up for outcome analysis. Data will be analyzed using SPSS (version 25) to compare gender disparities in management and outcomes using multivariable regression and survival analyses.

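### The abstract promises multivariable regression and survival analyses of the sex comparison, but the Statistics section specifies only unadjusted two-sample tests by gender

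*Protocol article*

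**What the plan says.** Two places in the article describe how women and men will be compared.

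- **Abstract, Methods.** The data will be analysed to "to compare gender disparities in management and outcomes using multivariable regression and survival analyses".
- **Statistics.** For categorical variables: "To compare frequencies based on gender, the Pearson chi-square test will be used when the application conditions are verified", with Fisher's exact test otherwise. For quantitative variables: "To compare means based on gender, the Student 2-tailed *t* test for independent samples will be used" under normality, and "If at least one variable is not normally distributed, the Mann-Whitney *U* test will be used". It adds that "data will be stratified by gender during analysis" and that P "values of less than .05 will be considered statistically significant".

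The Statistics section names no regression model, no covariate and no time-to-event method, and no other section of the body supplies one. Registry Objectives makes the comparison of diagnosis, treatment and outcomes between the sexes the primary goal. Clinical Assessment and Data Collection lists the variables an adjusted analysis would need: age, risk factors, prior events and comorbidities. It also states: "Key laboratory data such as creatinine and hemoglobin levels are also collected to assess renal function and anemia status".

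**The concern.** Sex is not randomised. Women and men who enter a registry through four different diagnoses can be expected to differ in age, diagnosis, comorbidity and renal function, and these can bear on both treatment and prognosis. The hypothesis is that women receive less appropriate care than men and fare worse as a result. That is a claim about comparable patients, which a crude difference in proportions does not address. Case mix can create such a difference, hide it or reverse it.

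Stratifying by gender does not help, because gender is the exposure. It only separates the two groups being compared. Strengths and Limitations mentions selection bias and infrastructure but not case-mix confounding, while Anticipated Findings expects the analyses to confirm disparities. If the crude tests were taken as the primary analysis, the main conclusion of the registry could rest on case mix.

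**Working it through.** **Comparing the two descriptions**

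| Element | Abstract, Methods | Statistics |
|---|---|---|
| Management by sex | multivariable regression | chi-square or Fisher; t or Mann-Whitney |
| Outcomes by sex | multivariable regression and survival analyses | no time-to-event method named |
| Covariates | implied by a multivariable model | none named |

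An abstract normally shortens the body. Here it names methods that the body's own Statistics section lacks, so this is a discrepancy inside one document and not only detail left to an unseen analysis plan.

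**How large the effect of case mix could be**

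The article gives no power, effect size or rates, so there is no stated figure to reproduce. The following is an illustration.

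Inputs from the article: a target of at least 2,000 women in Tunisia (Study Design) and 15,366 enrolled (Results). The sex split is not stated. Three splits are assumed: 2,000 and 2,000; 2,000 women and 15,366 − 2,000 = 13,366 men; and 15,366 / 2 = 7,683 per sex.

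Other assumed inputs: two case-mix strata, with treatment given to 70% in stratum A and 50% in stratum B **in both sexes**. Stratum A holds 55% of men and 45% of women.

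Crude rates:
- Men: 0.55 × 0.70 + 0.45 × 0.50 = 0.61
- Women: 0.45 × 0.70 + 0.55 × 0.50 = 0.59
- Crude gap: 0.02, although sex has no effect within either stratum

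Rejection rate of the unadjusted two-sided 0.05 test, counting rejections in the direction of the bias: Φ((0.02 − 1.96 × SE₀) / SE₁), with SE₀ the pooled and SE₁ the unpooled standard error.

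- 2,000 per sex: SE₀ ≈ SE₁ ≈ √(0.60 × 0.40 × 2/2,000) = 0.01549. Expected z = 0.02/0.01549 = 1.29. Φ(1.29 − 1.96) = 0.25.
- 2,000 women and 13,366 men: SE₀ = 0.01171, SE₁ = 0.01178. Φ((0.02 − 0.02295)/0.01178) = Φ(−0.25) = 0.40.
- 7,683 per sex: SE₀ ≈ SE₁ ≈ √(0.60 × 0.40 × 2/7,683) = 0.00790. Expected z = 2.53. Φ(2.53 − 1.96) = 0.72.

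A simulation of 4,000 studies per split compared the crude test with a Mantel-Haenszel test stratified by case mix:

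| Women / men | Crude test, formula | Crude test, simulated | Stratum-adjusted, simulated |
|---|---|---|---|
| 2,000 / 2,000 | 25% | 27% | 4.8% |
| 2,000 / 13,366 | 40% | 41% | 5.3% |
| 7,683 / 7,683 | 72% | 72% | 4.8% |

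**Range.** With stratum imbalances of 5 to 15 points and treatment-rate differences of 10 to 30 points, the crude rejection rate by the formula runs from about 5% to 85% with 2,000 per sex, 6% to 98% with 2,000 and 13,366, and 9% to nearly 100% with 7,683 per sex.

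**The case against.** The strongest reply is that the Statistics section never says its tests are the only analyses. The abstract of the same article commits to adjusted and survival analyses for exactly this comparison. The section can be read as covering the descriptive and bivariate step and leaving out the modelling step. This stands, and it makes the bias conditional. It does not remove the discrepancy: the section does state inferential tests and a threshold, and the modelling appears nowhere else in the body.

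A reader might infer more than the article supports:

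- **That confounded results will be reported as disparities.** This follows only if the Statistics section is the operative plan.
- **That the four diagnoses are pooled in one crude test.** The section does not say so. Treatment data sit in a diagnosis-specific part of the case report form, which suggests comparisons within diagnosis.
- **That 1-year events will be analysed by chi-square, ignoring censoring.** The section speaks of frequencies in general and assigns no test to follow-up events. The only statement on survival methods, in the abstract, points the other way.
- **That spurious differences are bound to be highly significant at this sample size.** That depends on the assumed imbalance and on the full enrolment split evenly, which is the most favourable split for significance. Comparisons within one diagnosis, or in a smaller cohort, have fewer patients.

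Two further points stand. Crude comparison is legitimate for describing insurance and income by sex, which is a secondary objective. The choice of effect measure and the fine detail of the models can be left to an analysis plan.

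**Conclusion.** The concern holds as a discrepancy that needs correcting: the promised adjusted and time-to-event analyses are missing from the section that fixes the tests. The mismatch is certain from the text. The bias is conditional on the Statistics section being what is run. It concerns the treatment, diagnostic and outcome comparisons, not the description of insurance and income.

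The size given above shows the mechanism and does not forecast the registry's results. Every rate, stratum share and sex split in it is assumed, and at the mild end of the range the crude test departs little from its nominal level. The point still matters because it affects the primary comparison.

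**What to change.** Amend the Statistics section so that it agrees with the abstract:

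1. Make the primary between-sex comparison of each treatment or diagnostic indicator within the relevant diagnosis, by a regression that reports an adjusted effect with its 95% CI. Use covariates already on the case report form: age, diagnosis, prior events, comorbidities, creatinine and hemoglobin.
2. Add insurance, income or socioeconomic status, and education only in a second model. The Hypothesis section treats socioeconomic factors as part of the route by which women's care suffers, so adjusting for them in the primary model would remove part of the disparity under study. The second model shows how much of the gap they account for.
3. Analyse 1-year events by the time-to-event methods that the abstract already promises.
4. Keep the chi-square, Fisher, t and Mann-Whitney tests as descriptive, including for the insurance and income objective.

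The cost is revised wording and a little more analysis work. No new patients are needed, and the listed covariates are already collected. Some crude differences may shrink after adjustment. If the abstract's analyses are already intended, the change is only a matter of stating them.

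### Means are compared by sex with the Student t test on a normality condition alone; where group sizes and SDs both differ by sex, its true level departs from the stated 5%, a minor point that naming the Welch test resolves at no cost

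*Protocol article*

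**What the plan says.** The Statistics section of the protocol article sets a decision rule for quantitative variables. First, "the Kolmogorov-Smirnov normality test will be performed for quantitative variables". For means by sex it then names the two-tailed Student t test, on one condition: the "test for independent samples will be used when the 2 quantitative variables are normally distributed". The fallback also depends on normality only: "If at least one variable is not normally distributed, the Mann-Whitney" U test replaces it. The threshold is P "values of less than .05 will be considered statistically significant". The section names no variance condition, no Levene test and no unequal-variance version of the t test. The software is SPSS version 25.

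On group sizes, the Abstract (Methods) describes enrolment of consecutive patients. The only target tied to sex is in Study Design: "The study aims to enroll at least 2000 female patients from Tunisia". No target for men and no ratio of women to men is given. The Results section reports that "By July 2023, a total of 15,366 participants had been enrolled across 25 centers", without a breakdown by sex.

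**The concern.** The pooled-variance t test needs equal variances as well as normality, unless the two groups are of about equal size. The rule checks only normality. Nothing in the design makes the groups equal, and within one of the four diagnoses the split may lie further from 1:1 than in the whole cohort.

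If the smaller group has the larger SD, the pooled standard error is too small and false positives exceed 5%. If the smaller group has the smaller SD, the standard error is too large and the test is conservative. The distortion depends on the ratio of the group sizes, not on their total, so 15,366 patients give no protection. It also arises with perfectly normal data, so it is separate from how normality is checked.

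At stake is the accuracy of P values for sex differences in means, in a study whose primary goal is to compare women with men.

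**Working it through.** **Inputs from the article:** two-sided level 0.05 (Statistics); total enrolment 15,366 (Results).

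**Inputs assumed, because the article does not give them:** the share of women (50%, 45%, 40%, 30%) and the ratio r of women's SD to men's SD (0.8 to 1.25). Men's SD is set to 1.

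**Formulas,** with n_w women and n_m men:

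- Variance the Student test uses: V_pooled = [((n_w − 1)r² + (n_m − 1)) / (n_w + n_m − 2)] × (1/n_w + 1/n_m)
- True variance of the difference: V_true = r²/n_w + 1/n_m
- True two-sided level = 2 × [1 − Φ(1.96 × √(V_pooled/V_true))]

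**The stated figure first.** With r = 1 at any split, or with a 1:1 split at any r, V_pooled = V_true and the level is 5.0%. The article's 0.05 is reproduced under those conditions.

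**Worked case, 30% women, r = 1.25.** n_w = 4,610 and n_m = 10,756.

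- Pooled variance = 1.1687, so V_pooled = 3.622 × 10⁻⁴
- V_true = 1.5625/4,610 + 1/10,756 = 4.319 × 10⁻⁴
- V_pooled/V_true = 0.8386, with square root 0.9157
- 1.96 × 0.9157 = 1.795, which gives a level of 7.3%

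**Results over the assumed range:**

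| Women | r = 0.8 | r = 0.9 | r = 1.0 | r = 1.1 | r = 1.25 |
|---|---|---|---|---|---|
| 50% | 5.0% | 5.0% | 5.0% | 5.0% | 5.0% |
| 45% | 4.5% | 4.8% | 5.0% | 5.2% | 5.5% |
| 40% | 4.1% | 4.5% | 5.0% | 5.4% | 6.1% |
| 30% | 3.2% | 4.1% | 5.0% | 5.9% | 7.3% |

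At a more extreme ratio of 1.5 and 30% women, the level is 9.3%.

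**Sample size does not help.** Simulation with 200,000 normal data sets per setting gave 3.3% (r = 0.8) and 7.2% (r = 1.25) for 60 women against 140 men. At 30% of 15,366 the simulated values were 3.3% and 7.2% as well.

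**The Welch test.** In the same simulations it lay between 4.9% and 5.1% in every setting tried: 50%, 40% and 30% women of 15,366, and 60 against 140 patients, with ratios from 0.8 to 1.5.

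**The other branch.** With 300 women and 700 men and normal data, the Mann-Whitney test rejected in 3.7%, 6.1% and 7.5% of 3,000 runs at ratios 0.8, 1.25 and 1.5. It is also off its nominal level when spreads differ.

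**How often the t test is reached.** Exactly normal data rounded to whole units, as age in years would be, were put through the Kolmogorov-Smirnov check. In two separate simulations normality was rejected in about 60% and 67% of runs at 1,000 per group, and in about 100% at 2,000 per group. In whole-cohort comparisons most variables will therefore go to Mann-Whitney. The t test will be used mainly in smaller subgroups.

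**The case against.** The case against has four parts.

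1. **The size is unsupported.** Neither the split nor the SDs are in the article, and with a near-equal split or similar SDs the error is negligible: 4.8% to 5.2% at 45% women with ratios 0.9 to 1.1. This stands. It limits what can be claimed about magnitude, but not the observation that the rule lacks a condition its test needs.

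2. **The branch is seldom reached and the main hypotheses lie elsewhere.** Kolmogorov-Smirnov will reject normality for most variables at cohort size. The expected disparities in imaging, procedures and guideline therapy are mostly proportions, tested by chi-square or Fisher. The Abstract also plans multivariable regression and survival analyses. This stands too, and is why the point is minor.

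3. **Which SPSS row is read belongs in an analysis plan.** SPSS prints the unequal-variance row by default, and *equal variance* is the usual meaning of Student's test rather than a phrase in the text. This stands in part. However, the article states a complete selection rule with named tests and conditions, and that rule names Student's test and only normality. It leaves the choice between two printed P values open at best.

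4. **A larger effect might be inferred, wrongly.** A reader might divide 2,000 women by 15,366 participants, take women as 13% of the cohort, and arrive at a true level near 10%. The article does not support that. The 2,000 is a minimum count for Tunisia, while 15,366 is total enrolment across 25 centers; their quotient is not a stated share of women.

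A reader might also conclude that the registry's P values are wrong. That does not follow either: they are off only where size and spread both differ by sex, by an amount and in a direction the article does not fix.

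**Conclusion.** The point holds as a minor one. The Student test is selected on normality alone in a design that does not fix the sex ratio, so its level is not assured at 5% wherever SDs differ by sex. Across the assumed 30% to 40% women and SD ratios of 0.8 to 1.25, the level runs from 3.2% to 7.3%; with 40% women and ratios of 0.9 to 1.1 it stays between 4.5% and 5.4%. These figures rest on assumed splits and SD ratios and on reading *Student* in its usual pooled-variance sense. No particular result is shown to be wrong. The practical reach is mainly comparisons of means within smaller diagnosis subgroups.

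**What to change.** In the Statistics section, replace the Student t test with the Welch unequal-variance t test for every comparison of means by sex. In SPSS 25, always read the row labelled *equal variances not assumed*, without a Levene pretest, and report the mean difference with its 95% CI from that row.

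The cost is a change of wording. No new data or software are needed, and at these sample sizes the loss of efficiency when variances are in fact equal is negligible. Fixing the row in advance also removes a choice between two P values after the data are seen.

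This change does not correct the Mann-Whitney branch, which will carry most whole-cohort comparisons of quantitative variables.
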